### 2.7. Privacy and Data Protection

The study protocol was submitted to the Territorial Ethics Committee of the Autonomous Province of Trento (PAT) for clinical trials in the early months of 2025 and was approved under number A1061 of 05/03/2026.

At the time of enrollment, all women who voluntarily choose to participate will be asked to sign an informed consent form following a detailed explanation of the study objectives, expected level of involvement, study duration, and ethical aspects related to data confidentiality. Additionally, participants will be provided with a privacy statement outlining how personal data will be collected, managed, and processed, as well as the participants’ rights under applicable data-protection regulations.

Informed consent—including consent to the processing of special categories of personal data—must be given freely, voluntarily, explicitly, and in written form prior to participation. Copies of both the informed consent form and the privacy policy will be provided to each participant and will remain accessible within the app throughout the study.

Personal data will be processed solely for research purposes. The functionalities of the platform and the virtual coach are specifically designed to support the psychological well-being of pregnant women. All collected data will be treated as confidential; only data necessary for the evaluation of the study’s objectives will be processed, and these will be pseudo-anonymized prior to analysis.

The study coordinator is committed to preparing a comprehensive final report and to ensuring that all data are reported in a responsible and consistent manner. Personal data will not be disclosed or disseminated, except in anonymized or aggregated form. The results of the study will be published regardless of outcome, and dissemination through scientific publications, conference presentations, or seminars will occur exclusively in anonymized and aggregated formats that prevent any direct or indirect identification of participants.

The final results will be made publicly available one year after the conclusion of the study.

### 2.8. Data Analysis

#### 2.8.1. Quantitative Analysis

Statistical data processing will be conducted using R software, version 4.0.0 [42], IBM SPSS Statistics, version 27.0 [43], Stata 17 [44], and JASP, version 0.18.2 [45].

Categorical variables will be summarized using absolute and percentage frequency distributions, while quantitative variables will be described through appropriate measures of central tendency and variability.

Descriptive analyses will be conducted for both the physical–psychological variables (including depressive and anxiety symptoms, general well-being, experiential avoidance, psychological flexibility, physical activity, and eating habits) and the usability (UX) and user engagement (UE) variables. These analyses will be performed on data collected at the start, during, and at the conclusion of the interaction with Demetra.

The relationships between variables will primarily be examined using specific statistical tests such as the chi-square test, Fisher’s exact test, paired *t*-test, Wilcoxon’s non-parametric tests, and the sign test (depending on whether assumptions are met). This will help identify differences between baseline and post-intervention measurements within the same sample for the variables under study. Additionally, univariate logistic or multinomial regression models will be presented. To control for potential confounding variables, multivariate regression models will be employed, adjusting the effects of explanatory variables on outcome variables accordingly. A *p*-value ≤ 0.05 will be considered statistically significant for all analyses. Furthermore, McNemar’s test and Cochran’s Q test are planned for assessing paired qualitative data [46].

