### 2.4. Sample Size Estimate

It was estimated that for this proof-of-concept study, it will be necessary to recruit 50 volunteer pregnant women. This sample size was determined considering that both parametric and non-parametric statistics will be performed.

According to Noether [23], when assuming a non-normal distribution, non-parametric statistical analyses require a sample size of 24 pregnant women, considering the Bonferroni correction (α = 0.025), desired statistical power, and appropriate effect size for non-parametric tests such as the Kruskal–Wallis test and Wilcoxon post hoc test [24].

If parametric statistical analyses are also planned (assuming a normal distribution), a sample size of 41 pregnant women is required, accounting for the Bonferroni correction (α = 0.025), with a statistical power of 0.80 and a significance level of 0.025. Considering a potential dropout rate of 20%, it is estimated that a total of 50 pregnant women should be recruited for the study.

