The Patient Health Questionnaire-9 (PHQ-9) and the Generalized Anxiety Disorder-7 (GAD-7) were chosen to measure depressive and anxiety symptoms, respectively, as these emotional states can interfere with the adoption of healthy behaviors and are relevant targets for ACT processes such as acceptance and cognitive defusion. The General Health Questionnaire-12 (GHQ-12) was included to provide a broader measure of general psychological well-being and functioning, complementing the PHQ-9 by assessing non-specific distress; the use of both tools allows for a more nuanced understanding of participants’ mental health status and distinguishes between general distress and specific depressive symptomatology. The Multidimensional Psychological Flexibility Inventory (MPFI) was selected as the primary theoretical outcome, as it directly assesses the six core processes of the ACT Hexaflex model, which the intervention aims to enhance. Two additional instruments, the MEDI-LITE and the International Physical Activity Questionnaire (IPAQ), assess adherence to the Mediterranean diet and physical activity levels, respectively, which are explicit behavioral targets of Demetra’s healthy lifestyle component and relate to the ACT process of committed action. The remaining four tools—User Engagement Scale—Short Form (UES-SF), System Usability Scale (SUS), Chatbot Usability Scale (BUS-11), and the User Mobile Application Rating Scale (uMARS)—were included to measure user engagement, usability, and perceived quality of the digital platform and the virtual coach. These usability and engagement metrics are critical in a feasibility study, as they inform the potential for sustained use and successful integration of ACT-based content into everyday life. This integrated battery of instruments allows for the simultaneous evaluation of psychological, behavioral, and technological engagement outcomes, providing a comprehensive picture of the feasibility and acceptability of the intervention.

An overview of the questionnaires and their administration schedule is provided in Table 2.

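### Section 2.4 sizes the study at a Bonferroni alpha of 0.025, but section 2.8.1 calls p ≤ 0.05 significant everywhere, with no correction

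*Protocol article*

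**What the plan says.** Section 2.4 (Sample Size Estimate) gives two calculations. The non-parametric one arrives at 24 women, "considering the Bonferroni correction (α = 0.025), desired statistical power, and appropriate effect size for non-parametric tests". The parametric one arrives at 41, "accounting for the Bonferroni correction (α = 0.025), with a statistical power of 0.80 and a significance level of 0.025". An allowance for 20% dropout then leads to 50 recruits. No effect size is given, sidedness is not stated, and the comparisons that share the corrected alpha are not named.

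Section 2.8.1 (Quantitative Analysis) plans paired t, Wilcoxon and sign tests of baseline against post-intervention values, along with regression models, McNemar's test and Cochran's Q. It closes the matter of significance with one rule: a p-value "≤ 0.05 will be considered statistically significant for all analyses". It mentions no Bonferroni step, no adjusted p-values and no family of tests.

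Section 2.6.2 and Table 2 list six questionnaires given at week 0 and again at week 6. Of these, the MPFI "was selected as the primary theoretical outcome, as it directly assesses the six core processes" of the ACT model.

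**The concern.** The two sections state different thresholds for the same tests. The rule in 2.8.1 covers every analysis without exception, so it cannot be read as leaving room for the 0.025 in 2.4. A paired test on one of these scores that returns p = 0.04 fails under the design and passes under the analysis rule.

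The correction in 2.4 was presumably meant to limit false-positive claims in a one-group study with several outcomes, and 2.8.1 removes that protection. If the conflict is still open when results arrive, someone will choose the threshold with the p-values in view. This is a contradiction in the printed text, so a later analysis plan could only settle it by overriding one of the two sentences.

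**Working it through.** **Inputs.** From 2.4: planning alpha 0.025, power 0.80, 41 evaluable women (parametric), 24 (non-parametric), 20% dropout, 50 recruited. From 2.8.1: analysis alpha 0.05. From 2.6.2 and Table 2: six pre/post questionnaires. Assumed, because the protocol does not say: a two-sided paired t-test, a standardised mean change d over a range, and one test per questionnaire.

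**1. Can the plan's 41 be reproduced?** Power is the probability that a noncentral t variable with n − 1 degrees of freedom and noncentrality d√n exceeds the critical value t(1 − α/2, n − 1). The smallest n with power of at least 0.80 is:

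| Assumed d | two-sided 0.05 | two-sided 0.025 |
|---|---|---|
| 0.40 | 52 | 62 |
| 0.45 | 41 | 50 |
| 0.50 | 34 | 41 |
| 0.55 | 28 | 34 |
| 0.60 | 24 | 29 |

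The 41 matches alpha 0.025 if d = 0.5. It also matches two-sided 0.05 if d = 0.45, and one-sided 0.05 if d = 0.40. So 41 is compatible with the alpha stated in 2.4, but it does not reveal which effect was assumed. The 24 cannot be checked without an effect size.

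For dropout, 41 × 1.2 = 49.2, which rounds up to the plan's 50. Dividing instead, 41/0.8 = 51.25, gives 52. That difference does not affect this point.

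**2. How many tests does 0.025 cover?** Taking 0.05 as the overall level, 0.05/0.025 = 2 tests.

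**3. Family-wise error**, as 1 − (1 − α)^m for m independent tests with no true change:

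| m | at 0.05 | at 0.025 |
|---|---|---|
| 2 | 1 − 0.95² = 9.75% | 1 − 0.975² = 4.94% |
| 6 | 1 − 0.95⁶ = 26.5% | 1 − 0.975⁶ = 14.1% |

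Scores from the same women will be correlated. In a simulation of six normal test statistics with pairwise correlation 0.5, the figure for six tests at 0.05 falls to about 21%.

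**4. Effect on power**, at n = 41 and assumed d = 0.5: 0.805 at alpha 0.025 and 0.878 at 0.05. The looser threshold raises power.

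**5. What a correction over all six questionnaires would need.** At 0.05/6 = 0.0083 and d = 0.5, 52 evaluable women, or 52/0.8 = 65 recruited. The planned 50 do not support that, so the choice is between two named tests and an openly exploratory analysis.

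**The case against.** The strongest objection is that little depends on these p-values. Sections 1.3.1 and 1.3.2 make co-design, experience and engagement the primary objective and the pre/post scores secondary. Section 2.6.2 says the questionnaires have no diagnostic purpose and serve description only. The Discussion grants that changes may have causes other than the intervention, and the Limitations state that effectiveness is not being evaluated. This stands, and it lowers the severity. It does not remove the conflict: the protocol still powers hypothesis tests, runs them and sets a significance rule for them. If the scores are purely descriptive, that blanket rule is what should go.

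One could also suppose that adjusted p-values will be compared with 0.05, which would reconcile the sections. Nothing in the document says so.

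Several stronger readings are tempting, and the documents do not support them:

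- **A chance finding is likely.** For six tests the figures are 21% to 26%, and these two-sided rates also count chance worsening. For improvement alone, with independent tests, the figure is 1 − 0.975⁶ = 14%. Counting the 12 MPFI dimensions plus five other scores as 17 independent tests gives 1 − 0.95¹⁷ = 58%, but the protocol never says each dimension will be tested, and subscales of one questionnaire are not independent.
- **A false positive would trigger the randomised trial.** The Discussion announces that trial without a condition. The Conclusions speak of encouraging results from a feasibility and usability study. Neither ties the decision to a significant score.
- **The study loses power.** Step 4 shows the reverse.
- **The protocol assumed d = 0.5.** That value is back-solved, and step 1 shows that others fit.

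**Conclusion.** The contradiction is real and rests on the text alone: 0.025 for planning and 0.05, uncorrected, for every analysis. Its consequence is a doubling of family-wise error for the two tests that the correction could cover (9.75% against 4.94%, independent tests) and 21% to 26% across the six questionnaires at one test each. Applying 0.025 to all six would still leave 14.1% if they are independent, so restoring that threshold works only if it is attached to two named comparisons.

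Under an assumed d = 0.5, the corrected alpha accounts for 41 − 34 = 7 evaluable women whom the rule in 2.8.1 would not require. That count depends on the assumption and should not be read as the protocol's own figure.

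Severity is moderate. The point should be settled before any data are analysed, but it does not touch the primary objective.

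**What to change.** Reconcile 2.4 and 2.8.1 before data are analysed, in one of two ways.

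**(a) Keep the correction.** Name the two pre/post scores to be tested at 0.025. The MPFI flexibility and inflexibility scores are one natural choice, given the status section 2.6.2 gives that instrument, but that status does not make it a primary endpoint and the sponsor may choose others. Replace the blanket 0.05 sentence so that all other scores are reported as change with a 95% confidence interval, labelled exploratory, with no claim of significance. State the effect size behind the 41.

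**(b) Drop the correction.** Remove Bonferroni from 2.4, restate the sample-size justification at 0.05 with its effect size, and label all pre/post tests exploratory and unadjusted for multiplicity.

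Either way the edit is a sentence or two in each section, and enrolment stays at 50. Under (a), 41 evaluable women have power 0.805 if d = 0.5. Under (b), 41 is the requirement at d = 0.45 and exceeds the 34 needed at d = 0.5. The cost of (a) is that fewer results can be called significant. The cost of (b) is that a small p-value carries no confirmatory weight.

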#### 2.8.2. Qualitative Analysis

Regarding the analysis of the semi-structured interviews, a text-mining approach will be employed to identify recurring responses related to women’s experiences interacting with Demetra and their feelings throughout the process. Additionally, qualitative methods such as thematic analysis will be applied to the focus group data.

Preliminary data analysis is scheduled for autumn 2025, with the final results expected at the study’s conclusion. The findings will be published within one year following the completion of the study

## 3. Expected Results

The psychoeducational pathway delivered through the virtual coach Demetra, integrated within the TreC Mamma app, is expected to have, first and foremost, significant results in terms of women’s satisfaction and engagement with the use of the innovative digital solution. Between the pre- and post-intervention period, it is expected to increase levels of physical and psychological well-being, women’s quality of life, and weight maintenance within their growth curve.

Importantly, Demetra can serve as a valuable resource by offering consistent psychoeducational support to women throughout and after pregnancy. Moreover, existing literature shows that women in the perinatal period often prefer online support, indicating that digital interventions can help overcome barriers related to social stigma and reluctance to seek help. Finally, it is essential to emphasize that Demetra and TreC Mamma are not intended to replace clinical or medical care but rather to complement these services by promoting physical and psychological well-being during pregnancy.

## 4. Discussion

This study aims to explore and assess women’s experiences and engagement with the TreC Mamma app and the virtual coach Demetra. Primarily, we seek to gather valuable feedback and suggestions from participants to enhance the intervention’s design, making it more engaging and improving user interaction. Additionally, we aim to observe potential differences in psychological well-being and healthy lifestyle behaviors before and after the intervention. However, we acknowledge that such changes may not be solely attributable to the intervention, and a randomized clinical trial will be conducted subsequently to rigorously evaluate its effectiveness.

All results will be reported and adequately discussed, including through a comparison with the relevant literature.

### Limitations

This study has several limitations that must be acknowledged and addressed when planning future studies. Firstly, as previously mentioned, it is important to note that the aim of this study is not to evaluate the effectiveness of the intervention; this is why a control group was not planned. In an RCT study, it will be crucial to involve a control group to assess actual effectiveness. Furthermore, the present study involved pregnant women from the Autonomous Province of Trento in Italy. Including participants from other Italian regions—and potentially other countries—would enhance the generalizability of the findings.

Secondly, the administration of multiple questionnaires may lead to participant overload, potentially affecting the quality of the collected data due to reduced motivation or rapid, unreflective responses. In addition, female participants will be recruited through hospital services by clinical staff without applying randomization or representative sampling methods, which may introduce a self-selection bias—participants may be more motivated or already familiar with digital technologies. Additionally, the follow-up period will cover only one month post-intervention, with no assessments during the postpartum phase, limiting the evaluation of long-term effects on lifestyle or psychological well-being. Lastly, although participants will be required to have sufficient knowledge of written and spoken Italian, their digital literacy will not be assessed. This may disproportionately affect women from certain social groups, potentially leading to early withdrawal from the study due to technical difficulties rather than lack of interest.

It is also important to highlight that Demetra can offer valuable technological support by providing regular psychoeducational services to women during pregnancy. Research has shown that women in the perinatal period often prefer online support, indicating that digital interventions can help overcome barriers such as social stigma and hesitation to seek help. Finally, it is essential to stress that these technological tools—Demetra and TreC Mamma—are not intended to replace clinical or medical care, but rather to complement them by supporting psychological and physical well-being throughout pregnancy.

## 5. Conclusions

The current literature emphasizes the increasing popularity of online support among women during the perinatal period and highlights the potential of digital interventions to overcome barriers related to social stigma and seeking help. Pregnancy is also an ideal time to focus on ourselves and find the motivation to change habits and improve lifestyle and physical activity. In this context, Demetra emerges as a promising resource, offering consistent psychoeducational support to help women change their habits and improve their lifestyle throughout pregnancy.

One crucial point to emphasize is that this protocol concerns a feasibility and usability study. If the results of this study are encouraging, as we expect, the next step will be to refine the intervention based on the feedback received during this study and design the next one, which, in our opinion, should be a controlled, randomized study to evaluate the effectiveness of the intervention. Once this step has also been completed, we can consider designing a real-world study to evaluate not only efficacy but also effectiveness.

A further step forward that will be essential to take will be to design the same intervention in different languages, making adjustments not only linguistically but also based on the culture of the participants.

## Figures and Tables

**Figure 1 ijerph-23-00483-f001:**
[figure not shown]
Overview of the intervention, including timing indications.

**Table 1 ijerph-23-00483-t001:** Summary of the questions of the qualitative interview.

Interaction	How did you find the interaction with the chatbot? Were there enough alternatives among the answers to be given to the chatbot? Which feature of the interaction did you like the most? And the one you liked the least?
Content	Do you feel that the mode of communication (length of sentences, terms used) was appropriate to the content?
Engagement and consistency	Was communicating with the chatbot engaging? In other words, did it encourage you to participate?
General	Do you have any concerns? Do you have any criticisms? Do you think that overall the intervention is suitable for a pregnant woman? from 0 to 10? When do you think would be the ideal time to have this intervention (beginning, middle, or end of pregnancy)?

**Table 2 ijerph-23-00483-t002:** Summary of the questionnaires administered and their timing.

At the Start of the Study (Week 0)	At the End of Week 3	At the End of the Study (Week 6)	Follow-Up (One Month After the End of the Intervention)
PHQ-9		PHQ-9	
GAD-7		GAD-7	
GHQ		GHQ	
MPFI		MPFI	
MEDI-LITE		MEDI-LITE	
IPAQ		IPAQ	
	UES-SF	UES-SF *	
	SUS	SUS *	
	ITA BUS B	ITA BUS B *	
		uMARS *	
			qualitative interview

Note. * These usability questionnaires will be administered the day after those investigating psychological variables, so as not to burden the participant during compilation.

## Data Availability

No new data were created or analyzed in this study.

## Abbreviations

The following abbreviations are used in this manuscript:

ACT	Acceptance and Committed Therapy
CBT	Cognitive Behavioral Therapy
PAT	Autonomous Province of Trento
APSS	Autonomous Province of Trento and the Provincial Healthcare Services
FBK	Bruno Kessler Foundation
ORBIT	The Obesity-Related Behavioral Intervention Trials
UX	User experience
UE	User engagement
BMI	Body mass index
SPID	Public Digital Identity System
CIE	Electronic identity card
PHQ-9	Patient Health Questionnaire-9
DSM-IV	Diagnostic and Statistical Manual of Mental Disorders, Fourth Edition
DSM-5	Diagnostic and Statistical Manual of Mental Disorders, Fifth Edition
GAD-7	General Anxiety Disorder-7
GHQ	General health questionnaire
MPFI	Multidimensional Psychological Flexibility Inventory
MEDI-LITE	Mediterranean Diet Adherence Questionnaire
IPAQ	International Physical Activity Questionnaire
BUS-11	Chatbot usability scale
SUS	System usability scale
UES-SF	User Engagement Scale—Short Form
uMARS	User Mobile Application Rating Scale
